# A Game-Based School Program for Mental Health Literacy and Stigma Regarding Depression (Moving Stories): Protocol for a Randomized Controlled Trial

**DOI:** 10.2196/11255

**Published:** 2019-03-14

**Keywords:** depression, help-seeking behavior, helping behavior, health literacy, stigma, video games, adolescence, secondary schools

## Abstract

**Background:**

The prevalence of elevated depressive symptoms among youth in most western societies is high. Yet, most adolescents who are experiencing depressive symptoms do not seek help. Low mental health literacy, high stigma, and low social support have been shown to hinder help-seeking. A small number of interventions has been developed to target mental health literacy and stigma, but few focus on actual help-seeking and first aid behavior. We have developed a game-based school program called Moving Stories that targets mental health literacy, including knowledge and behavior, and stigma among adolescents, in regard to depression specifically.

**Objective:**

Our aim is to describe the protocol for a study that will test the effectiveness of the program Moving Stories in a Dutch adolescent sample. We hypothesize that adolescents who participate in the program Moving Stories will have better mental health literacy and less stigma regarding depression compared to adolescents in the nonintervention control group at posttest and at 3- and 6-months follow-up. We also expect a positive change in actual help-seeking and first aid behavior at 3- and 6-months follow-up.

**Methods:**

Moving Stories has been developed by a professional game design company in collaboration with researchers and relevant stakeholders. The effectiveness of Moving Stories will be tested through a randomized controlled trial with two conditions: Moving Stories versus control. Participants will fill in questionnaires at pretest, posttest, and 3- and 6-months follow-up. Our power analysis showed a required sample size of 180 adolescents.

**Results:**

Four high schools have agreed to participate with a total of 10 classes. A total of 185 adolescents filled in the pretest questionnaire. The last of the follow-up data was collected in December 2018.

**Conclusions:**

If Moving Stories proves to be effective, it could be implemented as a school-based program to target mental health literacy and stigma regarding depression; this could, in turn, improve early help-seeking in adolescents suffering from depression.

**Trial Registration:**

Nederlands Trial Register NTR7033; https://www.trialregister.nl/trial/6855

**International Registered Report Identifier (IRRID):**

DERR1-10.2196/11255

## Introduction

### Background

Depression is considered to be one of the leading causes of disability worldwide. A recent World Health Organization report indicated that 4.4% of the world population is suffering from a depressive disorder [1]. Although the prevalence of depressive disorders in youth is lower than in adults [1], the numbers of young people experiencing elevated depressive symptoms are substantial. In a recent large-scale European study, approximately 40% of adolescents were suffering from clinical or subclinical depressive symptoms [2], which put them at increased risk for developing a depressive disorder in adulthood [3,4]. Furthermore, in adolescence, both symptoms of depression as well as a full-blown depressive disorder have been related to academic problems [5,6], social problems [5], physical problems, [5] and suicidal ideation [4]. In view of these long-term negative consequences, it seems important that young people seek the help they need to deal with depressive symptoms.

Even though many young people are experiencing depressive symptoms, over half of them do not seek help [7]. Some of the barriers to help-seeking are low mental health literacy, perceived stigma, and a preference for self-reliance [7,8], while social support and encouragement by others to seek help are related to increased help-seeking [7]. It is important to overcome these barriers and encourage social support, as prolonged time between depression onset and actual treatment leads to a diminished response to treatment and a smaller chance of remission [9]. Considering the high prevalence of depressive symptoms, the negative consequences, and the benefits of seeking help early in the process, it is relevant to target the causes that hinder help-seeking behavior in young people. Consequently, we have developed Moving Stories, a game-based school program that targets both mental health literacy and stigma regarding depression in young adolescents.

### Mental Health Literacy and Stigma

Mental health literacy has been defined as “knowledge and beliefs about mental disorders which aid their recognition, management, or prevention” [10]. Mental health literacy does not only refer to knowledge, but also to connected actions [11], not only by those who need help, but, equally important, by the people close to them.

With regard to recognizing a disorder, multiple studies have shown that both adolescents and adults find it difficult to recognize a mental health disorder [11,12]. Compared to adults, adolescents seem to be even less able to identify a disorder like depression [13]. Therefore, especially in adolescents, it is crucial that symptom and disorder recognition improve, as symptom recognition has been linked to choosing appropriate help and treatment [14].

Although increasing people’s ability to recognize a depressive disorder is beneficial for help-seeking behavior, labeling a person as mentally ill has also been linked to stigmatizing attitudes [15]. These attitudes, in turn, have been linked to a diminished amount of appropriate help being offered to peers in need of help [16], possibly counteracting efforts to increase help-seeking. Stigma is also considered to be an important factor as to why people who could benefit from help do not seek help or do not fully participate in treatment [17]. Consequently, this means that in targeting symptom recognition it is also necessary to focus on stigma.

One of the coping strategies that people with mental problems often use is finding social support. Most people view this type of help as potentially beneficial, but it becomes a concern when they turn solely to friends and family instead of seeking professional help [11]. Adolescents prefer seeking help from people they know [18,19] and they believe this help to be beneficial [20]. For adolescents, seeking help only from peers becomes a specific concern, since peers might not be able to provide sufficient or appropriate help [11]. Hence, adolescents could benefit greatly from knowing more about help-seeking options and available treatments. Moreover, teaching adolescents how to help their peers in learning about appropriate first aid for mental health could encourage the seeking of appropriate help among those who need it.

### Mental Health Literacy and Stigma Interventions

Although the research on mental health literacy interventions for youth is scarce, the few existing studies show promising results [12]. One example is of a school-based intervention consisting of short educational sessions in the classroom, involving a trainer who has lived experience with a mental disorder [21]. In a sample of 14-16-year-olds from the United Kingdom and Canada, findings showed an increase in mental health literacy after receiving the intervention. A second school-based intervention with lived-experience trainers targets symptom and disorder recognition with information-delivery sessions, videos, and discussions. This intervention proved to be effective in improving symptom and disorder recognition in Australian adolescents between 14 and 18 years of age [22]. A third school-based mental health literacy program consists of 10 hours of class sessions about mood disorders and helping peers, with teachers providing the program. The program was associated with increased mental health literacy and decreased stigma in Australian 13-16-year-olds [23].

More recently, teen Mental Health First Aid was developed [24]: an adolescent version of the well-studied Mental Health First Aid training for adults [25]. A recent meta-analysis demonstrated that the adult training results in a decrease of negative attitudes and an increase of knowledge and supportive behaviors toward others with mental health problems [26]. For the recent adolescent version, a Delphi consensus study was conducted to find key messages to use in the training to help adolescents provide basic mental health first aid to their peers [27]. Based on those findings, a 5-point action plan was developed that serves as the basis for the training. The first two effect studies showed promising results, with mental health literacy increasing and stigma decreasing in participating adolescents [24,28].

The research on mental health literacy interventions is scarce, but more work has been conducted on the effectiveness of antistigma programs. Most studies on decreasing stigma among youth reveal that education and contact with a person with lived experience—someone who has suffered from a mental health disorder him- or herself—are related to decreases in stigma [29]. A meta-analysis showed that education and contact were equally effective in decreasing stigma [29], while a review showed that personal contact was more important in reducing stigma among young people [30].

Even though there are promising programs for mental health literacy and stigma among youth, there are still few interventions that target actual help-seeking behavior. Most intervention programs focus on enhancing knowledge, but not on enhancing behavioral styles [11]. We have developed a game-based school program called Moving Stories. While most mental health literacy programs consist of didactic sessions, we argue that the nature of video games fits better with our goal of teaching skills alongside increasing knowledge. Already, there are several examples of video games successfully teaching youth health knowledge and skills (eg, in cancer treatment specifically [31] and healthy lifestyles in general [32]) and changing mental health stigma [33]. Games provide the opportunity to practice behavior in a relatively safe, engaging, and virtual environment and to learn by doing [34]. Moreover, players usually receive immediate feedback on their actions in games, encouraging them to continue and learn more [35]. Finally, games are an important part of young people’s lives [36], making a game-based intervention relevant for this population.

### Objectives

The goal of this paper is to describe the protocol for a study that will test the effectiveness of the program Moving Stories in a Dutch adolescent sample by means of a randomized controlled trial. Our first hypothesis is that adolescents who participate in the Moving Stories program will have better mental health literacy and will endorse fewer stigmatizing attitudes regarding depression than adolescents who do not participate, both directly at posttest and at 3- and 6-months follow-up. Second, we expect a change in help-seeking and first aid behavior. At 3- and 6-months follow-up, we expect that adolescents in the Moving Stories group, compared to the control group, will have sought more help if they were experiencing depressive symptoms or provided increased appropriate first aid if they were in contact with a peer who was experiencing depressive symptoms.

## Methods

### Design

The effectiveness of Moving Stories will be tested within a randomized controlled trial with two conditions: Moving Stories versus a nonintervention control group (see Figure 1 for the flowchart of the study design). We have chosen not to include a third condition with an alternative program because there is currently no mental health literacy program for young adolescents available in the Netherlands. Classes within a school will be randomized to either condition to avoid skewed distribution of participants over the two conditions due to school effects. The outcomes will be measured by self-report at four assessment points: T1 (pretest, within one week before the start of the program); T2 (posttest, within two weeks after the end of the program); T3 (3-months follow-up); and T4 (6-months follow-up), with the exception of the behavioral outcomes, which will not be assessed during posttest.

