**Figure 5 figure5:**
[figure not shown]
Iterative design process for the development of Moving Stories. RCT: randomized controlled trial.

To verify that Moving Stories does not increase depressive symptoms or suicidal ideation in adolescents, the Child Depression Inventory (CDI) [37,38] was administered. At all assessment points, if adolescents had a score on depressive symptoms in the clinical range and/or suicidal intention (CDI>29 and/or a score of 2 on question 9 of the CDI) [37,38], both the parents and adolescent were contacted by phone by a clinically trained member of the research team to inform them of the result and to give advice on where to seek professional help. We follow standard Dutch guidelines, in which we refer adolescents and their parents to the appropriate professional channels of care, where they will receive an assessment and subsequent intake if necessary. No follow-up of this group will be initiated from the research team itself. This procedure was approved by the Research Ethics Committee and complies with Dutch care guidelines. Adolescents who were contacted were not excluded from participating in the study, since that would increase stigma. During analyses, we will check and, if necessary, control for the possible effects of contacting participants and referring them to care.

To make sure that all adolescents who seek help from teachers during the study receive the help that they need, all teachers were provided with an information booklet developed for this study that includes short practical tips on what they can do to help their students. The primary researcher informed the teachers and other professionals involved at the school about the study and the short practical tips at an information session. In addition, teachers had the opportunity to follow an e-learning program on suicidality and depression in youth. This program, called Mental Health Online [39], aims to improve knowledge and self-confidence in people working with youth and has been found to be effective [40]. For this study, the developers of Mental Health Online have added an information page on depression to the program, since the e-learning program mainly discusses suicidality in youth [41] (in Dutch).

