##### Beliefs About Help

Beliefs about help were assessed by asking whether the following 10 people would make person’s situation in the vignette *better*, *not better*, *not worse,* or *worse*: (1) boyfriend or girlfriend; (2) friend (not related); (3) parent; (4) other relative; (5) psychologist or social worker (outside school); (6) phone helpline; (7) general practitioner; (8) teacher; (9) school welfare coordinator or school counselor; and (10) religious leader (eg, priest, imam, or rabbi). They were also asked who of those 10 would be most helpful. The number of selected adult sources deemed to be helpful (*better*) will be used to calculate beliefs about appropriate help: the *other relative* category will be excluded, since it could include an adult *or* peer [24].

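### The control is called nonintervention, but both arms get study-provided teacher support and CDI-triggered calls, so the trial estimates the added effect of Moving Stories, which matters most for help-seeking behavior

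*Protocol article*

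**What the plan says.** The Design section of the protocol article sets the comparison as "Moving Stories versus a nonintervention control group", and the Abstract uses the same label. In Objectives the first hypothesis is framed against non-participants: "fewer stigmatizing attitudes regarding depression than adolescents who do not participate". The second hypothesis expects that, at 3 and 6 months, program pupils with depressive symptoms will have sought more help than controls.

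Allocation is by class: "Classes within a school will be randomized to either condition". Every participating school was asked for at least two classes to make this possible.

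The Procedure section then describes support with no restriction by arm:

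- Booklet: "all teachers were provided with an information booklet developed for this study". Its purpose is given as "To make sure that all adolescents who seek help from teachers during the study receive the help that they need".
- Information session: the primary researcher briefed teachers and other school professionals on the study and on the practical tips.
- E-learning: "teachers had the opportunity to follow an e-learning program on suicidality and depression in youth". This is an existing program to which a depression page was added for the study.
- Phone contact: at every assessment point, if a pupil scored CDI>29 and/or 2 on item 9, "both the parents and adolescent were contacted by phone by a clinically trained member of the research team", with advice on where to find professional help.

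The same section says that the effects of contact and referral will be checked and, if necessary, controlled for. It states no such check for the teacher support.

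**The concern.** A control described as nonintervention leads the reader to take the estimated effect as Moving Stories against nothing. In this trial, control pupils attend schools where staff have been briefed on helping pupils, and those over the trigger, with their parents, are called and told where to get care. What is randomized is Moving Stories on top of that support, against that support alone.

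At stake is the reading of the second hypothesis. If controls get more help because of the study's own support, a small or null difference in help-seeking behavior need not mean that the program does little in a school without such support. Conversely, a positive difference was obtained in schools with prepared staff. The Discussion considers implementing the program in schools to improve early help-seeking. Its limitations (contamination, unmeasured discussions outside the game, no objective behavioral measures) do not mention the shared support.

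**Working it through.** **1. What each arm receives.**

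| Component | Program classes | Control classes |
|---|---|---|
| Lesson, game, contact session | yes | no |
| Teacher booklet and information session | yes | yes |
| Optional teacher e-learning | yes | yes |
| CDI-triggered calls to pupil and parents | yes | yes |

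The Program section defines Moving Stories by the three parts in the first row only.

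**2. What the difference estimates.** Let μ be the mean outcome with neither program nor support, S the effect of the support, M the effect of the program without support, and I their interaction.

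- Control arm: μ + S
- Program arm: μ + S + M + I
- Difference: M + I

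S cancels, so the shared support does not by itself bias the comparison. The difference equals M only if I = 0. Testing I = 0 would need the two unsupported cells, μ and μ + M, which the trial does not have. A null result caused by supported controls means I < 0: the support already supplies part of what the program would have supplied.

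**3. Which outcomes the support can reach.** Help-Seeking Behavior asks pupils who report a problem whether someone helped them in the last three months, and who. It does not separate help provided from help sought. Its source list, shared with Beliefs About Help, includes parents, teachers, the school counselor, general practitioners and psychologists. A teacher's approach, or a parent acting after a call, can therefore register directly as the outcome. Most of the nine literacy and stigma measures, such as symptom recognition, personal stigma and social distance, have no evident route of this kind, because the booklet, session and e-learning address staff.

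**4. Sample size.** Inputs from the Sample Size section: d = 0.40, alpha .05, power 80%, correlations .50, mean class size 18, coefficient of variation .19, ICC .02. Assumed: a two-sided test, and a pretest to 3-month correlation of .50, which is not given.

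- Unadjusted n per arm: 2 × ((1.960 + 0.842)/0.40)² = 98.1
- Variance factor for one baseline and two follow-ups: (1 + .5)/2 − .25 = 0.50, giving 49.06, rounded up to 50
- Design effect: 1 + ((.19² + 1) × 18 − 1) × .02 = 1.353
- Classes per condition: 50 × 1.35/18 = 3.75, rounded to 4, plus 1 = 5, so 90 per arm and 180 in all

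The stated figures reproduce, and relabelling the control changes none of them.

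**5. Illustration only.** The article gives no value for I. If an interaction reduced the standardized difference, power with 90 per arm, no dropout and 10 − 2 = 8 degrees of freedom would follow from SE = √(2 × 0.50 × 1.353/90) = 0.123:

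| d | 0.40 | 0.35 | 0.30 | 0.25 | 0.20 |
|---|---|---|---|---|---|
| Power | 81% | 71% | 58% | 43% | 30% |

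These figures apply to the literacy and stigma scores for which the trial was sized, where such a reduction is least likely. They are not estimates for help-seeking behavior, which is asked only of pupils reporting a problem.

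**The case against.** A reader might infer that the trial cannot support any conclusion against no intervention, or that the control arm received a help-seeking intervention that biases the result. The documents do not support either reading. Support open to both arms cancels in the difference. The booklet and session went to staff, the e-learning was optional and already existed, and the calls reached only pupils over the trigger, a group of unstated size. The hypothesis itself compares with adolescents not taking the program, the procedures are openly described, and the protocol plans to check for effects of contact and referral. All of this stands.

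A reader might also note that two of the seven adult sources scored in Beliefs About Help are school staff and take 2/7 = 29% as the size of the problem. That is a count of items about who could help a vignette character. It says nothing about how far any score moved.

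Three things survive the objection. The label is inaccurate. The planned check as stated covers contact but not teacher support. And absence of interaction cannot simply be presumed, since program pupils are themselves pointed to the school welfare coordinator or counselor (Program section) in schools whose professionals were briefed by the study. That makes interaction plausible; it does not show it.

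**Conclusion.** The point holds as one of labelling and of what may be concluded. The randomized difference validly estimates the added effect of Moving Stories in schools with study-provided teacher support and CDI-triggered contact. Reading it as an effect against no support requires no interaction, which the trial cannot test. The consequence is mainly for help-seeking behavior at 3 and 6 months, where a null result could reflect supported controls. For most literacy and stigma outcomes the documents show no evident route. Bias from the shared support alone is zero; the size of any interaction is unknown and cannot be derived from the article. The conclusion rests on reading the Procedure text, which sets no limit by arm, as applying to both.

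The Discussion should also be reconciled with the Procedure: it presents combining the program with depression screening as a future step, although CDI scoring with referral advice already runs alongside the program here.

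**What to change.** Leave the safety procedures unchanged.

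- Describe the control as *no Moving Stories; study-provided teacher support and CDI-triggered contact in both arms*.
- State the conclusion, above all for help-seeking, as the added effect of Moving Stories in schools with that support, and list this among the limitations in the Discussion.
- Report the number of pupils contacted at each assessment point, by arm.
- Base the planned check and adjustment for contact on T1 contact status only. T1 is measured before the program starts; later contacts come after randomization and may be affected by the program, so adjusting for them could distort the effect.
- Excluding pupils flagged at T1 may be shown as a supplementary analysis, with the intention-to-treat analysis kept as main. It removes pupils who matter most for help-seeking, leaves in those contacted later, and does not estimate an effect against no support.
- Do not rescore the help outcomes without the teacher and counselor sources. Getting an adult involved is the game's end goal and one of the five taught skills, so dropping these sources would remove real program effect and correct no bias.

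The cost is wording, one table of contacts and a specified adjustment, all on data already collected. The downside is a narrower claim.
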